## Abstract

**Background:**

Adolescence is a critical stage for the development of self-care. Many adolescents use mobile apps to monitor and improve their health. Health information technology plays a significant role in the field of self-care. This article provides a protocol for a study to design and evaluate mobile applications for adolescent self-care.

**Methods:**

The present research is a combination of applied development study, methodological, and intervention experimental. This study will be done in three stages: The first stage is the design and evaluation of a mobile application for adolescent self-care. The second stage is, designing and evaluating the psychometric properties of the “Questionnaire for Measuring Adolescent Self-Care Performance.” This questionnaire will be used before and after using the application in the third stage. The third stage is determining the effectiveness of self-care interventions based on mobile applications among adolescents. The target group will be adolescents aged 10–19 from the schools of Amol City. In the first stage, the opinions of 30 people adolescents, parents, and experts will be used. In the second stage, the number of samples will be 10 times the number of items in the questionnaire. In the third stage, 50 people will be in the intervention group and 50 people will be in the control group. Descriptive statistics will be used for data analysis. Between-group and intra-group comparisons will be calculated about quantitative variables, independent t-test and paired *t*-test, and analysis of variance. The chi-square test and Fisher’s exact test will be used in SPSS 16 software to test the homogeneity of qualitative variables between the two groups.

**Discussion:**

In the first stage, based on the opinions received from the target group, a user-centered educational application for self-care of adolescents will be designed. In the second stage, after determining the validity and reliability, a questionnaire will be designed to measure the self-care performance of adolescents. In the third stage, using an intervention study for 3 months, the effectiveness of the training will be determined through the designed application. Our findings are scheduled for a full analysis, with expectations that analyses will be completed by September 2023.

## Introduction

Enjoying health and well-being is considered one of the basic human needs and rights. Self-care—the first step to health—means taking care of yourself [1]. The concept of self-care was first introduced in 1959 by Orem as the “Nursing care deficit theory of self” [2]. Self-care is a conscious, learned, and purposeful practice. In it, each person uses his acquired abilities and skills in such a way that he can take care of himself personally and independently and help maintain and improve his health [2, 3].

Self-care is known to be one of the health-promoting behaviors of all ages that increases the level of health and quality of life. Health in adolescence guarantees health in adulthood and the health of future generations of any society. One of the best approaches in the field of adolescent health is to pay attention to the concept of self-care and its principles, about the physical and mental development of adolescents [4]. Therefore, the need for education and adoption of self-care behaviors is of particular importance for adolescents. In addition, raising the level of awareness of children and adolescents about the harmful factors that exist around them and teaching them how to interact properly with pathogens can play an important role in vaccinating them against such injuries [3, 5].

Adolescence is the phase of life between childhood and adulthood, from ages 10 to 19. It is a unique stage of human development and an important time for laying the foundations of good health. Adolescents experience rapid physical, cognitive, and psychosocial growth. This affects how they feel, think, make decisions, and interact with the world around them. Despite being thought of as a healthy stage of life, there is significant death, illness, and injury in the adolescent years. Much of this is preventable or treatable. During this phase, adolescents establish patterns of behavior—for instance, related to diet, physical activity, substance use, and sexual activity—that can protect their health and the health of others around them, or put their health at risk now and in the future. To grow and develop in good health, adolescents need information, including age-appropriate comprehensive sexuality education; opportunities to develop life skills; health services that are acceptable, equitable, appropriate, and effective; and safe and supportive environments. They also need opportunities to meaningfully participate in the design and delivery of interventions to improve and maintain their health. Expanding such opportunities is key to responding to adolescents’ specific needs and rights https://www.who.int/health-topics/adolescent-health#tab=tab_1. Compared to developed countries, adolescents living in developing countries generally receive fewer life skills and self-directed education on how to improve lifestyles, and a large number of these adolescents suffer from several health and lifestyle problems such as They suffer from unhealthy food or malnutrition, iron deficiency anemia, inactivity, tooth decay, mood disorders, and poor communication (especially with the opposite sex) and life skills [6–8].

Developmental self-care needs are identified as “conditions related to human developmental processes or conditions and events that occur during various stages of the life cycle.” In adolescents and adults, self-care needs are ideally met through the practice of self-care. When a person’s self-care requirements are met through self-care practice, the goal of self-care is achieved, and when it is not met, there is a lack of self-care [9].

One of the most effective strategies is the use of e-health in the treatment and prevention of health problems in children and adolescents. According to the definition of the World Health Organization (WHO), e-health emphasizes the cost-effective and secure use of information and communication technologies (ICT) in health support, including health services, monitoring, education, knowledge, and related research [10]. Increasing interest in exploiting the capabilities of mobile technology to support health has led to the development of an interdisciplinary branch of mobile health that can support the provision and promotion of health [11]. Mobile health is the provision of health services through mobile phones and their applications. Mobile applications are the ones designed for electronic devices such as smartphones and tablets [12, 13].

Self-care is greeted with more acceptance in the form of health along with providing targeted services, non-stop and interactive. It can increase technical capabilities, that is, the ability to carry it anywhere and anytime and the ability to send information through social networks. It also provides individual feedback and is used as a tool to encourage physical activity and healthy diets as well as monitoring heart disease, diabetes, and asthma symptoms. Furthermore, it can send reminders regarding appointments. Quitting smoking, promoting sexual health, reducing the transmission of sexually transmitted diseases, and assisting with prenatal care are some of the other benefits of self-care [14]. These programs can reduce the cost of health care and promote prevention, management, and treatment of chronic diseases, therefore reducing hospital stays. It also increases the quality of the data gathered, which helps healthcare professionals make faster and more accurate decisions. With the increase in the range of health software, the provision of services by mobile health has developed [15, 16].

A study of a mobile app to promote good oral health behaviors by Scheerman et al. (2018) showed that users welcome and enjoy consulting the app. The “white teeth” program can be included in current orthodontic care. The “white teeth” program includes all the techniques that make it a unique and promising home program to promote oral health among adolescents with fixed orthodontics [17]. A study by Ahmadi et al. (2015) showed that by connecting patients to care providers anywhere and anytime, mobile technologies can quickly access information, reduce costs, facilitate remote care, and increase quality care efficiency [18].

Given the ever-increasing popularity of healthcare software and as part of customer health informatics, these applications have the potential to facilitate patient self-care through patient education, disease management, and tracking. In addition, these apps potentially increase motivational capabilities and improve drug adherence. On the other hand, what is vital for the development of effective self-care as well as health and disease management are supervision of health activities and conditions directly related to the individual’s health goals, understanding and applying areas affecting health activities as well as the latest technologies in the world [16].

The mobile applications available in and out of the country have merely focused on self-care for a specific disease such as diabetes or asthma or for a health problem such as obesity. According to the investigations, a comprehensive mobile application for physical self-care of adolescents was not found. Therefore, the aim of this study was to design a protocol for the design and evaluation of mobile application for adolescents’ physical self-care.

### General goals

This study has three general goals:Design and evaluation of a mobile application for adolescent self-care.Designing and evaluating psychometric properties of “Questionnaire for Measuring Adolescent Self-Care Performance.”Determining the effectiveness of self-care interventions based on mobile application among adolescents.

## Methods

The present study is a combination of developmental, applied, methodological, and field trials or studies and will be conducted in three stages. The first stage is to design and evaluate the initial version of a mobile application for adolescent’s self-care. The second stage is the design and psychometrics of a “Questionnaire for Measuring Adolescent Self-Care Performance.” The third stage is determining the effectiveness of the designed application in an interventional study. The target group of this study are adolescents aged 10–19 years old (Fig. 1).

**Fig. 1 Fig1:**
[figure not shown]
An overview of the study design

### Inclusion and exclusion criteria

Inclusion criteria are as follows: 10–19 years old, informed consent to participate in the study as well as the consent of their parents or legal guardians, having a smartphone and the ability to work with it. Exclusion criteria are as follows: unwillingness to continue cooperation and incomplete completion of the questionnaire.

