#### The third stage

The next stage of the sampling method is cluster random. From 337 government schools and 93 non-government schools, based on the list of urban schools received from the Department of Education, two boys’ schools and two girls’ schools are randomly selected. Then, one boy’s school and one girl’s school will be randomly assigned as the intervention group and one boy’s school and one girl’s school will be in the control group, and the sampling of students of different grades of the selected schools will be simple cluster or random. Sampling of students from different grades from selected schools will be simple in cluster or random. The sample size was calculated according to the formula of 43 people in each group. Taking into account 15% attrition, the sample size was determined to be 50 people in each group. The study will be conducted on 100 students of Amol City. Of these, 50 people will be assigned to the intervention group and 50 people will be assigned to the control group. From each school, 25 samples were selected (Fig. 2).

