#### Stage III

The third stage is an interventional method of experimental study. This research will be conducted through a pre-test-post-test design with a control group. All the students studying in schools constitute the research community. The researcher first introduces the adolescents to the full explanation of the research and its goals. Then informed written consent will be obtained from the volunteers. None of the participants will be subject to any other research intervention. Schools will be randomly assigned to one of the two intervention (group 1) and control (group 2) groups. The full content of the program will be visible only to the participants in the intervention group. Participants in the control group will be able to download the app after the end of the intervention to use the educational benefits of the app. A self-care application can be used online and offline designed for smartphones running the Android operating system. To run this test, eligible students are asked to install the self-care app on their smartphone and see the necessary instructions on how to work with the program in the form of a short guide on the main page of the application. Initially, the participants are asked to complete the self-care questionnaire in the form of a pre-test. Then, the educational content designed for the application is provided for individuals based on national and international guidelines and protocols of (WHO, CDC, FDA, ADF, Ministry of Health and Medicine, Health Education and Health Promotion Office). This program will be available to people for 3 months and after installing the application on their smartphone and entering the information requested from the users, educational content and reminder messages will be sent according to their conditions. In the reminders section, the user registers his health behavior based on the day, time, and number of times he wants, and a reminder is sent to him. But if the user’s self-care status after answering the self-care questions in each of the 5 dimensions of self-care is assessed as weak or average, motivational health messages are sent to the user daily in the form of notifications, so that the user is encouraged to perform self-care behaviors. The use of the application by the participants is reviewed in the management panel and health messages and incentives are provided for the use of this program. To provide support, the researcher’s phone number is given to the subjects to make a call in case of problems. Three months after the intervention, when no new content is sent to the student, the participants in both groups are requested to complete the self-care questionnaire in the form of a post-test. After the end of the data collection process, the individuals in the control group can install a mobile Application and the necessary training will be given to them after the end of the study. In the present study, content, information, and experiences reach the end users or audience with the specific purpose of self-care through mobile applications in the form of text, audio, or other art forms. Users find and use health-related self-care information through content. The graphic design of the application is based on the opinion of the research team professional designers and application development experts. The production of the content is based on the points extracted from the interviews, national and international guidelines, and protocols of (WHO, CDC, FDA, Ministry of Health and Medicine, Health Education and Health Promotion Office), for example, Australian dietary guidelines, Canberra: NHMRC [20], WHO guidelines on physical activity and sedentary behavior for children and adolescents aged 5–17 years: summary of the evidence [21], and physical activity guidelines [22].

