#### The third stage

At this stage, we use a researcher-made questionnaire the validity and reliability of which were determined in the second stage. The desired questionnaire is uploaded on the application and after installation, this program will be available to people for 3 months. After 3 months of the intervention, by an SMS or a phone call, the people of both groups are asked to complete the questionnaire uploaded, which is in the form of a post-test, and send it back to the researcher. After collecting the data, analysis is conducted by statistical tests.

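### Stopping cooperation and an incomplete questionnaire are listed as exclusion criteria, which leaves the stage 3 comparison open to bias of unknown size and direction

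*Protocol article*

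**What the plan says.** The protocol article has one list of criteria for all three stages (Inclusion and exclusion criteria). The exclusion part reads in full: "Exclusion criteria are as follows: unwillingness to continue cooperation and incomplete completion of the questionnaire". It is not limited to any stage or to the time before allocation.

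For stage 3, the unit of allocation is the school (Sampling method, The third stage): "Then, one boy’s school and one girl’s school will be randomly assigned as the intervention group", with one school of each kind as control. Pupils are sampled within those schools. Losses are expected: "Taking into account 15% attrition, the sample size was determined to be 50 people in each group".

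The questionnaire is the stage 3 outcome. It is completed as a pre-test and again after three months of app access, when "the people of both groups are asked to complete the questionnaire uploaded, which is in the form of a post-test" (Data collection methods, The third stage). That request goes out by SMS or telephone. During follow-up the arms are handled differently (Study process, Stage III): "The full content of the program will be visible only to the participants in the intervention group".

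Under Ethical considerations, participants may leave at any stage. Methods of analysis names t-tests and analysis of variance, and the sampling section adds a covariance adjustment for economic status and social class. Nowhere does the article say that pupils are analysed as allocated.

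**The concern.** An exclusion criterion normally describes a person at entry. Neither of these does. A pupil can be unwilling to continue only after joining, and the questionnaire is the outcome measure. Applied to stage 3, the rule decides who enters the comparison by what pupils do after their school has been allocated.

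Allocating schools protects the comparison only for the pupils enrolled under that allocation. If those removed differ between arms, in number or in how their self-care scores relate to leaving, the remaining groups are no longer comparable and the difference in means mixes the app's effect with selection. The arms have different experiences for three months, so different patterns of leaving are plausible.

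This is more than a missing-data method left to an analysis plan. The article states a rule, and an analysis plan that kept these pupils would contradict it.

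**Working it through.** **Step 1: when each criterion can act in stage 3.**
- Incomplete pre-test: after school allocation, before exposure to the content.
- Withdrawal during follow-up: after allocation and after exposure has begun.
- Incomplete post-test: after allocation and after the three months of access.

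The last two are the stronger cases.

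**Step 2: the article's own figure.** Inputs from Sampling method, The third stage: 43 per group, 15% attrition, 50 per group.
- 43 × 1.15 = 49.45, rounded up to 50.
- 43 / (1 − 0.15) = 50.6, rounded up to 51.

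The stated 50 is reproduced by the first route and is one below the second. Losing 15% of 50 leaves 50 × 0.85 = 42.5, so about 7 pupils per group are expected to be lost.

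**Step 3: the effect that 43 per group implies.** The article gives the formula but not alpha, power or Δ/S. Solving it for Δ/S with an assumed two-sided alpha of 5%, Δ/S = √(2(z₁₋α/₂ + z₁₋β)² / 43):
- 80% power: √(2 × (1.960 + 0.842)² / 43) = 0.60.
- 90% power: √(2 × (1.960 + 1.282)² / 43) = 0.70.

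**Step 4: shift from excluding pupils.** If a share f of an arm is excluded and those excluded score g SD below those retained, the retained mean exceeds the full-arm mean by f × g. With the same g in both arms, the shift in the difference is (f_intervention − f_control) × g. All values of f and g below are assumed.

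| Excluded, intervention v control | g = 0.25 SD | g = 0.5 SD | g = 1 SD |
|---|---|---|---|
| 15% v 15% | 0 | 0 | 0 |
| 15% v 5% | 0.025 | 0.05 | 0.10 |
| 25% v 5% | 0.05 | 0.10 | 0.20 |

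The 25% v 5% row averages to the article's 15% allowance. Swapping the arms reverses the sign.

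Equal rates do not guarantee safety. With 15% excluded in each arm, but g = 0.5 or 1 SD in one arm and 0 in the other, the shift is 0.15 × 0.5 = 0.075 or 0.15 × 1 = 0.15 SD.

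**Step 5: scale.** Over the unequal rows of the table, the shift runs from 0.025 / 0.70 = 4% to 0.20 / 0.60 = 33% of the implied effect. With 43 per arm and clustering ignored, the standard error is √(2/43) = 0.216 SD. If the app had no effect, the two-sided 5% error rate would become about 5 to 8% for 15% v 5% and 6 to 15% for 25% v 5%.

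**The case against.** The strongest reply is that nothing here shows bias, still less bias in favour of the app. Much of that stands. Four stronger readings are tempting, and the article does not support them.

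- *Unengaged intervention pupils are dropped while all controls are kept.* The criteria apply to both arms. Low app use does not trigger them: a pupil who ignores the app but returns a complete post-test stays in. Controls also take a pre-test, so they too can fall foul of the rule.
- *The bias favours the app.* Study process, Stage III gives intervention pupils burdens (data entry, daily motivational messages for those rated weak or average, review of their use). It also gives them incentives, reminders and a support telephone number. Controls have only later access to look forward to and could leave more often, which would reverse the sign.
- *One missing item discards the whole record.* Incomplete is not defined, so this is only one possible reading.
- *Losses are accepted and not followed up.* Both groups are contacted by SMS or telephone for the post-test, and inflating 43 to 50 is ordinary planning.

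It is also fair that the section serves all stages and that requiring a complete questionnaire is natural in the stage 2 psychometric work. The harm concerns stage 3, the only stage with allocated arms.

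Finally, imputation from the pre-test removes only the part of the bias that the pre-test explains, and pupils who withdraw consent cannot be pursued. These points limit what the fix can achieve. They do not justify keeping the exclusions.

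**Conclusion.** The point holds as a design weakness with unknown consequences. In stage 3 the two stated exclusions remove pupils after school allocation and, for withdrawal and the post-test, after exposure. No passage restricts them to the time before allocation or says that pupils are analysed in the arm of their school. The comparison is open to bias if exclusions differ between arms in rate or reason.

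Size and direction cannot be read from the article. The illustrative shift of about 0.03 to 0.20 SD, against an implied effect of about 0.60 to 0.70 SD, rests wholly on assumed exclusion rates, score gaps, power and alpha. It is zero if exclusions are alike in both arms. A reader might infer that the result is bound to be biased towards the app; the article gives no differential exclusion rate and no evidence on who would leave, so that inference is not supported.

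**What to change.** For stage 3:

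1. Limit exclusion criteria to characteristics known before allocation. A complete-questionnaire requirement can remain for stage 2 if it is labelled as such.
2. Treat withdrawal and incomplete questionnaires as missing data.
3. Request the post-test from every pupil who has not withdrawn consent, whatever their app use, through the SMS or telephone contact already planned.
4. Analyse all enrolled pupils in the arm of their allocated school.
5. Keep partly completed questionnaires under an item rule stated in advance.
6. Use the pre-test in the analysis or in the imputation of missing post-tests, with complete cases as a sensitivity analysis.
7. Report losses and reasons by arm, so that readers can judge the bias that remains.

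The cost is a change of wording, slightly more analysis work and one extra reminder.
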